## Abstract

**Background:**

The Internet can increase access to psychosocial care for breast cancer survivors through online support groups. This study will test a novel prosocial online group that emphasizes both opportunities for getting and giving help. Based on the helper therapy principle, it is hypothesized that the addition of structured helping opportunities and coaching on how to help others online will increase the psychological benefits of a standard online group.

**Methods/Design:**

A two-armed randomized controlled trial with pretest and posttest. Non-metastatic breast cancer survivors with elevated psychological distress will be randomized to either a standard facilitated online group or to a prosocial facilitated online group, which combines online exchanges of support with structured helping opportunities (blogging, breast cancer outreach) and coaching on how best to give support to others. Validated and reliable measures will be administered to women approximately one month before and after the interventions. Self-esteem, positive affect, and sense of belonging will be tested as potential mediators of the primary outcomes of depressive/anxious symptoms and sense of purpose in life.

**Discussion:**

This study will test an innovative approach to maximizing the psychological benefits of cancer online support groups. The theory-based prosocial online support group intervention model is sustainable, because it can be implemented by private non-profit or other organizations, such as cancer centers, which mostly offer face-to-face support groups with limited patient reach.

**Trial Registration:**

ClinicalTrials.gov: NCT01396174

## Background

Ongoing and timely access to relevant information and social support can improve psychological outcomes in breast cancer patients [1], but such access is far from universal [2]. The Internet can increase access to psychosocial care through online support groups (OSGs), yet the few randomized trials of cancer OSGs have yielded mixed results [3-6]. Thus, there is a need to develop innovative approaches to maximizing the psychological benefits of OSGs. An obvious benefit of a support group is access to information and emotional support from similar others. Less obvious are the benefits accrued from providing help to others. According to the "helper therapy principle," [7] helping benefits the helper, possibly enhancing psychological and physical health outcomes [8-11]. Based on this theory and prior research, we hypothesized that OSGs that maximize opportunities for providing help to others would be highly efficacious at reducing distress symptoms.

Depression and anxiety symptoms are highly prevalent among breast cancer survivors [12] and often undertreated [13]. A systematic review found high rates of probable depression in breast cancer patients (10% to 25%) [13]. In a rare 5-year cohort study, nearly 50% of women with early breast cancer had depression, anxiety, or both one year after diagnosis, 25% in the second, third, and fourth years, and 15% in the fifth year [14]. Controlling distress is important in its own right, but clinically it may be important to address psychological distress in breast cancer patients in the early years after treatment because it can be detrimental to quality of life, treatment adherence, cancer surveillance, health behaviors (e.g., exercise, diet), self-care (e.g., managing lymphedema), and overall health outcomes including risk for recurrence, and decreased immune function [12,15-19]. Breast cancer may bring about distress, in part, through its adverse effects on self-esteem [20], sense of social belonging [21], and sense of purpose [22,23]. Amount of helping others has been shown to be positively related to all of these outcomes and inversely related to depression [24,25]. Thus, an intervention promoting prosocial behavior might reduce distress in breast cancer survivors directly and indirectly through these psychological correlates of distress.

Dozens of interventions have been designed to reduce distress in cancer survivors, but the evidence on their efficacy and acceptability is weak [26,27]. Moreover, many interventions that require in-person contact are expensive and do not reach patients who might be constrained by time, money, mobility, or location. OSGs are a fairly low cost alternative to in-person interventions and overcome many of the obstacles of in-person interventions. Breast cancer survivors often use OSGs [28], so this population should be receptive to an OSG intervention.

To date, the evidence on the efficacy of cancer OSGs is limited. Winzelberg et al. [3] randomized 72 breast survivors to a professionally facilitated OSG or a wait-list control group. Compared with the controls, OSG participants had significantly greater reductions in depressive symptoms (effect size = 0.54) from baseline to follow-up. Fifty-three percent of OSG participants who were depressed at baseline were below the clinical cut-point at follow-up, compared with only 29% improvement in the control group. Owen et al. [6] randomized 62 breast cancer survivors to an Internet-based coping-skills training group (with access to a non-facilitated peer discussion board) or to a wail-list control group and found no intervention effects on quality of life. Similarly, Salzer et al. [4] randomized 78 breast cancer survivors to a non-facilitated OSG or to an Internet-based education control group and found no intervention effects on distress or quality of life. And, finally, Gustafson et al. [5] randomized 295 breast cancer survivors to a non-facilitated OSG or to a control group and found no intervention effects on quality of life. Given this mixed evidence, we cannot draw firm conclusions on the efficacy of cancer OSGs. The field must identify ways to maximize the psychological benefits derived from OSGs if they are to be recommended.

The current study will develop and evaluate a novel OSG intervention that theoretically should boost the benefits observed in standard facilitated OSGs [3,29]. Most social support research focuses on the health benefits of *receiving *social support [30], but there is evidence that *providing *social support also confers benefits [11,31-33]. Some research even suggests that providing support is more beneficial than receiving support [10,31]. In general, engagement in prosocial actions (e.g., helping, advising) appears to enhance health and quality of life outcomes [33,34]. However, the bulk of empirical evidence on the benefits of helping comes from observational studies with non-clinical populations. Studies using controlled experimental [35] or longitudinal observational designs [36] are rare. The current trial is the first to evaluate the psychological benefits of increasing helping behaviors among distressed cancer survivors in the context of an online supportive intervention.

The trial also aims to identify potential mechanisms underlying the psychological benefits of helping. Based on the literature and Midlarsky's [33] conceptual framework, we developed the model in Figure 1. The model identifies several potential mediating variables that have been linked both to helping behavior and to psychological distress. Helping has been positively correlated with self-esteem [37] and positive affect [38], which, in turn, have been negatively correlated with psychological distress [39,40]. The role of positive affect is of particular interest given the evidence that positive emotions do not just signal optimal psychological functioning, but they can produce it [41]. Positive emotions also can facilitate coping with stress [42]. Helping others also can increase a sense of belonging, or mattering to others [43], which, in turn, has been linked to lower levels of depression and anxiety [44,45]. Further, we anticipate that sense of belonging will be indirectly related to psychological distress through its effects on sense of purpose. The formation of interpersonal attachments has been called a fundamental human need [46]. Belonging to a group and having a role in that group can have a powerful influence on one's sense of purpose [47]. Cancer survivors often report a diminished sense of purpose and meaning in life [22,48]. In turn, a lack of purpose is associated with psychological symptoms of depression and anxiety [49]. If establishing meaningful connections with others can promote or restore a sense of purpose, it could also reduce distress [50].

**Figure 1 F1:**
[figure not shown]
**Conceptual model for Life Beyond Cancer trial**.

### Objectives and Hypotheses

The major objective of the "Life Beyond Cancer" trial is to test the efficacy, acceptability, and feasibility of a novel OSG for distressed breast cancer survivors that provides structured helping opportunities and coaching on how best to give support to others. The trial targets distressed breast cancer survivors because they will likely benefit more than non-distressed patients from psychosocial interventions [51]. The study will explore whether the enhanced OSG increases the exchange of helping behaviors among distressed breast cancer survivors and, consequently, reduces their psychological distress symptoms and increases their sense of purpose relative to their counterparts in a standard OSG. Secondarily, we will evaluate potential psychological mediators of the enhanced, prosocial OSG, and evaluate the acceptability and feasibility of implementing the prosocial OSG among distressed breast cancer survivors.

Hypothesis 1: Relative to women in the standard OSG (S-OSG) condition, women in the prosocial OSG (P-OSG) condition will have a lower mean level of depression/anxiety symptoms at posttest.

Hypothesis 2: Relative to women in the S-OSG condition, women in the P-OSG condition will have a significantly greater mean level of sense of purpose in life, self-esteem, positive affect, and sense of belonging at posttest.

Hypothesis 3: Positive increases (posttest-pretest) in mean level of self-esteem, positive affect, and sense of belonging will partially mediate the effects of the P-OSG intervention on mean level of depression/anxiety symptoms and sense of purpose at posttest.

Hypothesis 4: Positive increases (posttest-pretest) in mean level of sense of purpose will partially mediate the effects of the P-OSG intervention on mean level of depression/anxiety symptoms at posttest.

Hypothesis 5: Given the equal level of attention across conditions, we hypothesize that there will be no significant between group differences in retention (percent completing study) and mean level of satisfaction with the intervention.

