### Analytic Plan

Descriptive statistics will be generated for the total sample and the treatment groups for each time point. Distributional properties will be analyzed to determine if variance stabilizing or normalizing transformations should be applied. Outliers will be assessed and checked for accuracy. Non-response and attrition must be addressed in longitudinal research [71]. Therefore, full information maximum likelihood (FIML) and multiple imputations (MI) will be used to correct for missing data [71]. Variables associated with missing data mechanisms will be included as covariates in models or used to create multiple imputations as appropriate. Both FIML and MI are implemented in a variety of software packages including LISREL, AMOS, and MPlus, each of which can accommodate all statistical models (ANCOVA, OLS and logistic regression, mediation models, etc.) that will be estimated in this project.

Hypotheses 1 and 2: Post-test differences between P-OSG and S-OSG in primary and secondary outcomes will be tested using ANCOVA, with intervention group as the predictor and appropriate pre-test scores as covariates. Intent-to-treat analyses will be used. Variance associated with cohort membership will be estimated via intraclass correlation coefficients. If necessary cohort can be entered into the ANCOVA models as a random effect or fixed-effects analyses can be performed if there is evidence for unobserved heterogeneity. Group-level analyses can be performed on aggregate data if necessary.

Hypotheses 3 and 4: Mediation will be tested in a series of ANCOVA models using standard statistical software or structural equation modeling software. Hypothesis tests will be based on bootstrapped standard errors [72].

Hypothesis 5: Acceptability will be assessed by recruitment and retention rates, reasons for refusal/dropout, and level of participants' ratings of satisfaction and helpfulness of different intervention elements. Fisher's exact test will be used to evaluate differences between conditions for categorical outcomes; t-tests or non-parametric equivalents can be performed to compare ordinal or continuous outcomes.

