The feasibility of manipulating online helping behavior will be assessed by comparing mean levels of observed helping behaviors (using SOL data) enacted by participants in the P-OSG versus S-OSG and participants' willingness and ability to generate a "helping blog" and engage in "outreach" activities in the P-OSG condition. Additional analyses will be conducted to confirm that treatment fidelity was equivalent across conditions and to explore dose-response relations by examining whether level of participation (e.g., attendance, number of posts, amount of help provided to others) moderates intervention effects.

Because this is a preliminary study of the effect of the novel P-OSG intervention, we are interested in estimating effect sizes of the P-OSG intervention group. More specifically, we are interested in gaining an estimate of the true treatment effect size (which is independent of sample size) and to establish a plausible confidence interval around this effect size. Thus, we present information regarding the aim of accuracy in parameter estimation (AIPE) [73] as well as information relevant to the aim of null hypothesis significance testing.

AIPE identifies a range (half-width, *w*) within which an effect size can be bracketed with a specified probability, independent of the magnitude of the observed effect size. It is easiest to interpret in the metric of standardized regression coefficients, i.e., β ± *w*. For these analyses, AIPE will depend on (a) the number of predictors, (b) variance in predictor of interest accounted for by other predictors, $R_{xx}^{2}$, and (c) overall variance predicted in outcome, $R_{yx}^{2}$. Our models will have between 2 (pre-test & treatment) and 10 predictors (i.e., adding 3 mediators and possibly 5 cohort identifier dummy variables). We estimated half-widths assuming: model $R_{yx}^{2}$ was either high (.5) or low (.1) and $R_{xx}^{2}$ was zero (treatment), low (.1) or high (.5). With 80% probability for N = 180 (90 per experimental condition), we expect to be able to bracket effect sizes for treatment effects within ± .11 to ± .15 depending on model R^2^. Effect sizes for mediators will be estimated with somewhat less precision but within ± .12 to ± .22

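### H3 and H4 use mediator change scores, apparently without the baseline mediators; if posttest level drives the outcome, the indirect effect is understated and full mediation can look partial

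*Protocol article*

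**What the plan says.** Under Objectives and Hypotheses, H3 states: "Positive increases (posttest-pretest) in mean level of self-esteem, positive affect, and sense of belonging will partially mediate the effects of the P-OSG intervention". H4 states: "Positive increases (posttest-pretest) in mean level of sense of purpose will partially mediate the effects of the P-OSG intervention". The mediators are therefore changes, while depression/anxiety symptoms (H3 and H4) and sense of purpose (H3) are outcomes measured as posttest levels.

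In the Analytic Plan, H1 and H2 are tested by ANCOVA "with intervention group as the predictor and appropriate pre-test scores as covariates". For H3 and H4 the text says only: "Mediation will be tested in a series of ANCOVA models using standard statistical software or structural equation modeling software". It names no covariates for those models. On inference it adds: "Hypothesis tests will be based on bootstrapped standard errors".

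The precision calculation in the same section does list model terms: "Our models will have between 2 (pre-test & treatment) and 10 predictors (i.e., adding 3 mediators and possibly 5 cohort identifier dummy variables". It assumes N = 180 and gives half-widths of ±.12 to ±.22 for mediator coefficients. The protocol states no size for any indirect effect, no pre-post correlation for a mediator, and no baseline correlation between a mediator and an outcome.

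**The concern.** A model with the change score M1 − M0 and no separate M0 term forces the baseline mediator's coefficient to be exactly minus the posttest mediator's coefficient. Nothing in the protocol tests or justifies that restriction. The Background argues in terms of levels (higher self-esteem, positive affect and purpose go with lower distress), and H2 analyses the same variables as posttest scores adjusted for pretest.

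If level is what matters, the mediator-outcome path is estimated too small. The total effect does not change, so the missing part reappears as a direct effect. Full mediation would then look partial, which is the pattern that H3 and H4 predict. At stake is the reading of the secondary mechanism aim. The H1 efficacy test is not affected.

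**Working it through.** **1. The plan's own figure.** The stated half-widths are reproduced by a 95% interval with 80% assurance:

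w = t(.975, N−p−1) × √[(1−R²yx)/((1−R²xx)(N−p−1))] × √[χ²(.80, N−1)/(N−p−1)]

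- N = 180, p = 10, R²yx = .5, R²xx = .1: w = .122 (stated .12).
- N = 180, p = 10, R²yx = .1, R²xx = .5: w = .219 (stated .22).
- Treatment, p = 2, R²xx = 0: .110 and .148 (stated .11 and .15).

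**2. The predictor count.** 1 pre-test + 1 treatment + 3 mediators + 5 cohort dummies = 10. A three-mediator model that also held the three baseline mediators would have 13.

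**3. Attenuation formula.** Let T be treatment, Y0 the pretest outcome, and D = M1 − M0. Given Y0 and T, let V0 and V1 be the variances of M0 and M1 and C their covariance. Suppose that the outcome depends on M1 with coefficient b and on M0 with coefficient λb. Using D without M0, the estimated path is b × [k − λ(1−k)], where

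k = (V1 − C)/(V1 + V0 − 2C).

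**4. Worked case (all values assumed).** Unit SDs, pre-post correlation r = .5, baseline mediator-outcome correlation |q| = .5, λ = 0:

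- V0 = 1 − .25 = .75
- V1 = 1 − .25 × .25 = .9375
- C = .5 × .75 = .375
- k = .5625/.9375 = .60, a loss of 40%

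With a = .4, b = −.4 and no true direct effect, the true indirect effect is −.160. The change-only model gives .4 × .60 × (−.4) = −.096, which leaves about −.064 as a direct effect. A simulation of 1,000,000 records gave −.096 and −.063. With M0 added, the change and posttest codings both gave −.160 indirect and about 0 direct.

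**5. How the loss moves with the assumptions.**

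- Equal SDs, λ = 0, r from .3 to .9: 50% at q = 0; 46–47% at |q| = .3; 38–41% at .5; 33–37% at .6; 26–31% at .7.
- |q| = .5, λ = 0, r = .5 and .7: 16–25% if the posttest SD is 1.2 times the baseline SD; 60–70% if it is 0.8 times.
- |q| = .5, equal SDs: about 60% at λ = +.5; about 20% at λ = −.5; 0% at λ = −1, where the outcome truly follows change.

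**6. Bootstrap test.** One mediator, N = 180, a = .4, r = .5; 300 data sets with 300 bootstrap samples each; Monte Carlo error about .02–.03.

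- b = −.4, baseline mediator included: power .81 with a z-test on the bootstrap SE, .85 with the percentile interval.
- b = −.4, change only: .62 and .77.
- b = −.2, baseline mediator included: .57 and .78, so the gap depends on the assumed path.
- a = 0: rejection .027–.037 with the SE test, .060–.063 with the percentile interval.

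The mean estimate is the same under either method.

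**The case against.** The strongest reply is that the omission is never stated. The mediation paragraph lists no covariates, ANCOVA normally implies baseline adjustment, and H2 already adjusts each mediator for its pretest. The 10-predictor count comes from a planning calculation in a condensed article, and three more terms would barely alter its result. For H4, with a single mediator, the ceiling of 10 would even leave room for baseline purpose. This stands as a reason to treat the omission as an inference. Even so, the listed terms, "adding 3 mediators and possibly 5 cohort identifier dummy variables", include no baseline mediator, and the change-score wording points the same way.

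A second reply is that H3 and H4 literally name change as the mediator, in which case nothing is lost. That is correct, but a model that includes the baseline mediator covers this case too, while the change-only model is right only under that one restriction.

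Third, the Background predicts both direct and indirect effects from theory, no decision rule separates full from partial mediation, and attenuation is conservative for claiming an indirect effect. This limits the consequence. It does not remove the distortion of the direct effect.

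Fourth, the text names no normal-theory test, so the z-test reading is also an inference. Part of the percentile interval's advantage comes from its being slightly liberal when a = 0.

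**Conclusion.** The point holds in conditional form. As written, the hypotheses and the predictor count imply mediation models without baseline mediators. If so, and if posttest level drives the outcome, the indirect effect can be materially understated and the direct effect overstated. The loss is about 40% under the assumptions of the worked case, and 0% to about 70% across the others tried.

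A reader might infer that the plan shrinks the indirect effect by a third to a half. The documents do not support this: that range needs equal SDs, no direct effect of the baseline mediator and |q| up to about .6, none of which they give. Nor do bootstrapped standard errors shrink anything. If they mean a z-test, the test is conservative for a product of two coefficients and loses some power.

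Mediators and outcomes share one posttest, so their order cannot be shown. That is a limit of the disclosed pretest-posttest design, and a reverse-order model would not resolve it.

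**What to change.** State that, for H3 and H4, each mediator's pretest value and the pretest outcome are covariates in both the mediator model and the outcome model. The mediator may then be coded as change or as posttest, since both give the same indirect effect. Update the predictor count to match.

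All variables are already collected. With three mediators the cost is three more predictors (13 instead of 10). Mediator half-widths go from .122–.219 to .124–.223 with R² held fixed.

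Separately, name percentile bootstrap confidence intervals for the indirect effects, and note that their rejection rate may be slightly high (about .06) when treatment does not move the mediator. This is a change of wording only.

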#### Prosocial online support group intervention

The P-OSG intervention includes elements of the S-OSG, but with critical modifications and key additions. First, participants will receive a tip sheet that describes how to recognize others' needs for different kinds of support and how to be helpful in an online environment. Second, the facilitator will post reminders at the beginning of each session on the importance of responding to one another's needs for help. Third, participants will be asked to commit to a goal of offering informational or emotional support to group members each week during the live synchronous sessions or later using the discussion board, email or chat. Fourth, prior to each week's meeting, participants will receive an email describing the topical problem to be discussed (e.g., pain, fatigue, and lymphedema). Their "homework" is to prepare 1-2 sentences on how their experiences with the problem might help others to cope with the problem. If they have not had the problem, they will be asked to write 1-2 sentences on how their approach to coping with other life problems might be useful to group members coping with the particular problem of the week. Fifth, the facilitator will encourage helping by highlighting direct and indirect requests for support by group members, will praise those who offer help (e.g., "Nice suggestion, Margie."), and will encourage additional help (e.g., "Has anyone else found a good way to cope with the problem Joan mentioned?").

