Members of the P-OSG also will be asked to select one of the six weekly topics to prepare a blog about the topic to share with the group. The goal will be to write about their experience as a way of helping other breast cancer survivors who have gone through a similar experience. The writing instructions will emphasize that participants should not worry about grammar or spelling and that if they wish the research staff can help to edit their writing for grammar or spelling before posting. Participants will be asked to blog about any effective ways they have developed to cope with a cancer-related problem. The exercise will emphasize that people often have experiential knowledge that is valuable to others, but can only be accessed if there is sharing. Bloggers will be told that the exercise is designed to help other patients to understand the different consequences of breast cancer and its treatment, as well as how they might best manage or address these consequences. Instructions also will explain that the bloggers do not necessarily have to provide answers or solutions to the problems they write about, they simply need to share their experience. Reading others similar experiences can help to normalize the experience or make readers feel less alone. We recognize that some participants might be resistant to sharing their writings with others, either because they do not feel it will be valuable or they feel it is too personal. We will offer individuals the opportunity to have their blog posted anonymously, or only post select information, or for us to paraphrase what they have written in a list of comments comprised of input from multiple blogs. All blogs will be fact checked by research staff to avoid posting misinformation.

Finally, in addition to promoting helping within the group, the P-OSG will promote helping outside of the group through an outreach activity called the "Breast Cancer Awareness Ambassadors" program. Women in the P-OSG group will be asked to increase breast cancer awareness by sharing a "Breast Cancer and You" fact sheet and "Mammograms Save Lives" e-Cards, both developed by the Centers for Disease Control and Prevention, with women in their social network who are 40+ years old.

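### Hypothesis 5 predicts a non-significant result and tests it with difference tests and no margin, so failure to reject would count as support for similar retention and satisfaction

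*Protocol article*

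**What the plan says.** Under Objectives and Hypotheses, the protocol article states Hypothesis 5 as: "Given the equal level of attention across conditions, we hypothesize that there will be no significant between group differences in retention". The prediction in full, with satisfaction included, is of "no significant between group differences in retention (percent completing study) and mean level of satisfaction with the intervention".

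The Analytic Plan paragraph on Hypothesis 5 assigns the tests: "Fisher's exact test will be used to evaluate differences between conditions for categorical outcomes", and "t-tests or non-parametric equivalents can be performed to compare ordinal or continuous outcomes". It also lists the wider evidence: "Acceptability will be assessed by recruitment and retention rates, reasons for refusal/dropout, and level of participants' ratings of satisfaction and helpfulness". No equivalence or non-inferiority margin, interval criterion or power figure is attached to this hypothesis. The precision and power statements later in the Analytic Plan, based on "N = 180 (90 per experimental condition"), concern treatment and mediator effects on the outcomes, not retention or satisfaction.

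On attention, the section on the standard group describes weekly facilitated sessions of about 1.5 hours, six topics, email and chat, and a private writing task that controls for the blog. The section on the prosocial group says: "The P-OSG intervention includes elements of the S-OSG, but with critical modifications and key additions".

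**The concern.** The predicted result is itself the absence of significance. A test of difference controls the risk of wrongly declaring a difference. It gives no control over the risk of wrongly inferring similarity. The smaller the sample, the more easily the prediction is borne out.

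Acceptability is part of the trial's stated major objective, so a reader of the results will look to this hypothesis to learn whether the prosocial format costs participants. If retention were materially worse in that arm, the plan as worded could still record the hypothesis as supported.

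The premise that attention is equal also needs care, because it is the only reason given for expecting no difference.

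**Working it through.** **Inputs from the article.** 90 per arm, 1:1 allocation, α = .05, satisfaction on 5-point scales.

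**Assumed, because the article gives no figure.** Retention in the standard group of 80% to 95%; a loss of 10 points in the prosocial group; satisfaction differences in SD units. Clustering by online group is ignored.

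**The plan's own figure first.** No figure is stated for Hypothesis 5. The nearest is the minimum detectable effect of .42 at zero pre-post correlation: (1.960 + 0.842) × √(2/90) = 0.418, or 0.420 with the noncentral t. This confirms 90 per arm and a two-sided 5% level.

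**Retention.** The exact power of Fisher's test is Σₓ Σᵧ Bin(x; 90, p₁) × Bin(y; 90, p₂) × 1[Fisher p ≤ .05]. The probability of a non-significant result is 1 minus this.

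| True retention, standard vs prosocial | Power | Non-significant |
|---|---|---|
| 95% vs 85% | 0.55 | 0.45 |
| 90% vs 80% | 0.40 | 0.60 |
| 85% vs 75% | 0.32 | 0.68 |
| 80% vs 70% | 0.28 | 0.72 |

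By interpolation, the chance of missing a 10-point loss falls below one half once standard-group retention passes about 93% to 94%.

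**Satisfaction.** Two-sample t-test with noncentrality d × √(90/2). For d = 0.3 this is 0.3 × 6.708 = 2.01, giving power 0.52, so the difference is missed with probability 0.48. For d = 0.2 it is missed with probability 0.73, for 0.4 with 0.24, and for 0.5 with 0.08. If only 72 per arm give ratings (an assumed 20% loss), a 0.3 SD difference is missed with probability 0.57.

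**What 90 per arm can say about retention.** The 95% half-width under equal retention p is 1.96 × √(2p(1−p)/90): 8.8 points at 90%, 10.4 at 85%, 11.7 at 80%.

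**Whether a margin would rescue the claim.** Take the usual equivalence rule, with the 90% Wald interval wholly inside the margin, and truly equal retention. Exact enumeration at 90 per arm gives:

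| Retention in both arms | Power, ±10 points | Power, ±15 points | ±15 points met despite a true 10-point loss from this rate |
|---|---|---|---|
| 90% | 0.46 | 0.91 | 0.26 |
| 85% | 0.20 | 0.76 | 0.21 |
| 80% | 0.06 | 0.62 | 0.19 |

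A ±10 margin is therefore usually inconclusive. A ±15 margin has better power, but would still pass a real 10-point loss about one time in four or five. Requiring the 95% interval inside ±10 points would be harder still: at 85% and 80% its typical half-width already exceeds the margin.

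**The attention premise, side by side.** Shared or matched: facilitated weekly sessions, the six topics, and a writing task in each arm. Described only for the prosocial arm: a tip sheet, session reminders to help, weekly helping goals, pre-session emails with homework, fact-checking of blogs by research staff (editing is optional), and outreach ("the P-OSG will promote helping outside of the group through an outreach activity called" the Breast Cancer Awareness Ambassadors program). The standard group's writing is seen by no one, including the research team.

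**The case against.** The strongest reply is that the article never says a non-significant p-value will be reported as proof of equality, and never speaks of equal acceptability. Acceptability is judged on several strands, of which the between-arm test is one. Hypothesis 5 gates nothing, its evaluation is introduced as secondary, and the study calls itself preliminary and interested in effect sizes with confidence intervals. Retention by arm will be visible anyway, and missing outcome data are handled by FIML and multiple imputation.

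Much of this stands. A reader might infer that one p-value will settle acceptability, or that differential dropout would go unnoticed; the text supports neither. A reader might also infer that the arms are matched only on private writing. That is wrong, since sessions, topics and facilitation are common to both.

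What does not fall is the hypothesis as worded. Its prediction is non-significance, the assigned tests are difference tests, and none of the other strands is given a rule that replaces non-significance for the between-arm comparison. An analysis plan that implemented the hypothesis as written would carry the problem over. The estimation stance elsewhere in the Analytic Plan argues for the change, since it is not extended to retention or satisfaction.

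**Conclusion.** The point holds in limited form. Hypothesis 5 lets failure to reject count as support for similarity. Under assumed standard-group retention of 80% to 90% and 90 per arm, a true 10-point loss would be non-significant in about 60% to 72% of trials. A 0.3 SD satisfaction difference would be missed about half the time.

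It is tempting to say that such a loss would usually be missed whatever the retention. The documents do not support that, because they give no rate: at 95% versus 85% it is missed 45% of the time. Larger satisfaction differences would mostly be found (0.5 SD in about 92% of trials).

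Nor do the documents show that the equal-attention premise is false. Core contact is shared; the premise is stronger than the described components allow. The matter concerns the interpretation of a secondary hypothesis and leaves the primary efficacy test untouched.

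**What to change.** 1. Restate Hypothesis 5 as estimation. Report the between-arm differences in retention and in mean satisfaction with 95% confidence intervals, and state that a non-significant test will not be read as no difference.
2. Claim similarity only if a margin for each measure is justified before posttest data are seen and the whole interval lies inside it, with the interval's confidence level fixed at the same time. Acknowledge that at 90 per arm a 10-point retention margin would usually be inconclusive (power about 6% to 46% at 80% to 90% retention with a 90% interval). A wider margin should not be chosen merely to gain power.
3. Soften the premise: say that sessions, topics and facilitation are shared and that writing is matched to the blog, and name the added prosocial components that have no described counterpart.

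The cost is rewording and two interval calculations, with no change to conduct or sample size. The downside is that the trial may be unable to claim similarity.
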